**Methods:**

This protocol describes a single-center, parallel-group, randomized controlled trial. Fifty-seven healthy female college students aged 18–22 years will be recruited from Fenyang College, Shanxi Medical University, and randomly allocated in a 1:1:1 ratio to a Tai Chi Chuan group (TCC), unstable resistance training group (URT), or Tai Chi Chuan combined with unstable resistance training group (T + URT). All interventions will last 8 weeks, with three 60-min sessions per week. The primary outcomes will be dominant-leg knee extensor peak torque, knee flexor peak torque, and hamstring-to-quadriceps ratio measured using an isokinetic strength testing system at 60 degrees/s. Secondary outcomes will include overall stability index, anteroposterior stability index, and mediolateral stability index under eyes-open and eyes-closed conditions measured with the Biodex Balance System. Assessments will be conducted at baseline and after the 8-week intervention. Intention-to-treat and per-protocol analyses will be used. Missing data will be handled using multiple imputation where appropriate.

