## Objectives and hypotheses

The primary objective is to evaluate the effects of an 8-week Tai Chi Chuan combined with unstable resistance training programme on knee flexor and extensor strength in female college students, compared with Tai Chi Chuan alone and unstable resistance training alone.

The secondary objective is to compare the effects of the three intervention modalities on dynamic balance capacity under eyes-open and eyes-closed conditions.

The main hypothesis is that the combined intervention will produce greater improvements in knee flexor peak torque, knee extensor peak torque, H/Q ratio, and dynamic balance indices than either single-modality intervention. A secondary hypothesis is that Tai Chi Chuan alone will show particular advantages in proprioception-dependent balance and H/Q optimization, while unstable resistance training alone will show particular advantages in rapid improvement of extensor strength.

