### Sample size

The sample size will be estimated using PASS 15.0 software. Knee extensor peak torque will be selected as the primary outcome for sample size calculation. Based on relevant preliminary and published experimental data, the expected mean and standard deviation of post-intervention knee extensor peak torque in the three groups will be used to estimate an effect size of Cohen’s *f* = 0.55. With a two-sided alpha level of 0.05, statistical power of 0.90, and one-way analysis of variance for three-group comparison, the minimum required sample size is 16 participants per group. Allowing for an anticipated dropout rate of approximately 15%, 19 participants will be enrolled in each group, yielding a total sample size of 57 participants (32).

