### Statistical analysis

Two analysis sets will be used. The intention-to-treat set will include all randomized participants in their originally allocated groups regardless of adherence or withdrawal. The per-protocol set will include participants who complete the full intervention protocol without major protocol deviations. The primary analysis will be based on the intention-to-treat principle, and the per-protocol analysis will be used as a sensitivity analysis.

Missing data will be handled using multiple imputation when the missingness mechanism is considered missing at random. Baseline knee muscle strength, dynamic balance index values, age, height, and weight will be considered predictor variables for imputation. Five imputed datasets will be generated using a multiple linear regression model in SPSS 25.0. Pooled estimates will be calculated according to Rubin’s rules. If missing data are minimal, complete-case analysis may be reported as a supplementary analysis.

Categorical variables will be expressed as n (%). Normally distributed quantitative variables will be presented as mean ± standard deviation, and non-normal data as median (interquartile range). Normality will be tested with the Shapiro–Wilk test, and variance homogeneity with Levene’s test. For within-group pre–post comparisons, paired t-tests will be used for normally distributed data; otherwise, Wilcoxon signed-rank tests will be applied. Between-group differences will be assessed using one-way ANOVA for parametric data, followed by Bonferroni-adjusted pairwise comparisons when the overall effect is significant. Non-parametric data will be analyzed with the Kruskal–Wallis test, followed by Dunn–Bonferroni pairwise comparisons. Categorical variables will be compared using the chi-square test or Fisher’s exact test. Given three primary outcomes (knee extensor peak torque, knee flexor peak torque, and hamstring-to-quadriceps ratio), a Bonferroni correction will be applied to control multiplicity, with a significance threshold set at *p* < 0.017 (0.05/3). Secondary outcomes are exploratory, a two-sided *p* < 0.05 will be used without multiplicity correction.

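### Single-step Bonferroni across the three primary outcomes is valid but gives away omnibus power that Holm's step-down would keep at the same family-wise error

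*Protocol article*

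**What the plan says.** The abstract lists the outcomes: "The primary outcomes will be dominant-leg knee extensor peak torque, knee flexor peak torque, and hamstring-to-quadriceps ratio". Table 5 gives the same three, with H/Q calculated from the two torques.

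Under Statistical analysis, each outcome is compared between arms by one-way ANOVA (Kruskal–Wallis if non-normal). Bonferroni-adjusted pairwise comparisons follow when the overall effect is significant. Across the three primary outcomes, "a Bonferroni correction will be applied to control multiplicity, with a significance threshold set at" p < 0.017 (0.05/3). For the balance indices the section adds: "Secondary outcomes are exploratory", tested at 0.05 without correction.

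Under Sample size: "Knee extensor peak torque will be selected as the primary outcome for sample size calculation". The calculation takes f = 0.55, two-sided alpha 0.05, power 0.90 and a three-group ANOVA. It gives 16 per group, or 19 enrolled per group after 15% dropout.

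Under Objectives and hypotheses, the primary objective concerns the effect of the "programme on knee flexor and extensor strength in female college students" and does not name H/Q. The sentence stating the main hypothesis reads in part: "the combined intervention will produce greater improvements in knee flexor peak torque, knee extensor peak torque, H/Q ratio, and dynamic balance indices". The comparison it makes is with each of the two single programmes.

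**The concern.** With three co-listed primary outcomes and one significance level to share, the plan holds every outcome to 0.05/3 whatever the other two show. Once one outcome has been rejected, only two null hypotheses can still be true, so the next test can be made at 0.05/2 and the last at 0.05 without raising the family-wise error. The fixed threshold gives that up.

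This matters more here because EPT was sized at 0.05 but will be judged at 0.05/3. Part of the planned power is already lost, and Holm recovers some of it without extra participants.

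The wording around the tests adds a smaller problem. The objective omits one of the three primary outcomes, and the main hypothesis places exploratory balance indices beside the confirmatory ones. A reader cannot tell from that section that claims are to be made one outcome at a time.

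**Working it through.** **Inputs.** From the protocol article: three primary outcomes, threshold 0.05/3, f = 0.55 on EPT, 16 evaluable per arm, one-way ANOVA on three arms. Assumed, because the article gives none: T + URT shifted above two equal single arms, EPT mean 100 (SD 15), FPT mean 58 (SD 9), EPT–FPT correlation 0.3 to 0.8, and a standardised FPT gain of 1, 1.5 or 2 times the EPT gain.

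**1. The plan's own figure.** Power comes from the noncentral F with lambda = f² × N and df = (2, N − 3). At alpha 0.05, 15 per group gives 0.9001 and 16 per group gives 0.920, so the stated 16 is adequate. Enrolment: 16/0.85 = 18.8, hence 19 per group and 57 in total, as stated.

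**2. Validity of the threshold.** 3 × 0.05/3 = 0.05 (0.0492 if the tests were independent), so the family-wise error is controlled. The printed 0.017 is 0.01667 rounded.

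**3. EPT power at each Holm level.** With N = 48, lambda = 0.3025 × 48 = 14.52 and df = (2, 45).

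| Level | EPT power |
|---|---|
| 0.05/3 | 82.5% |
| 0.05/2 | 86.4% |
| 0.05 | 92.0% |

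Bonferroni fixes EPT at the first row. Holm places it between the first and the last, depending on how many other outcomes have already been rejected.

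**4. Why Holm loses no rejection.** The ordered p-values are compared with 0.05/3, 0.05/2 and 0.05, stopping at the first failure. None of these limits is below 0.05/3, so any outcome with p < 0.05/3 passes its step and all earlier ones. The first step is the Bonferroni test of the smallest p, so the chance of at least one rejection is identical.

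**5. Size of the gain.** Simulation of 40,000 trials per setting. A single-arm shift of d = 3f/√2 = 1.167 SD gives f = 0.55, and H/Q is computed as FPT/EPT.

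| FPT gain relative to EPT gain | EPT, Bonferroni | EPT, Holm |
|---|---|---|
| 1 times | about 82% | about 85% |
| 1.5 times | about 82% | 88–90% |
| 2 times | about 82% | 91–92% |

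The ranges cover correlations 0.3 to 0.8. With no true effects, the family-wise error is the same for both methods, about 0.042 to 0.045. In a second set-up, with f = 0.55 on all three outcomes and common correlation 0, 0.5 or 0.8, power per outcome rises from about 82.5% to 90.5%, 88.9% or 87.7%.

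**6. What Holm does not improve.** For three equal arms, F = (t₁₂² + t₁₃² + t₂₃²)/3. If each pairwise test is held at 0.05/9, the critical t on 45 df is 2.91. T + URT beating both single arms then forces F ≥ (2/3) × 2.91² = 5.65, above the omnibus critical value of 4.49 at 0.05/3. Every such trial has therefore already passed under Bonferroni. Its probability for EPT is about 50% under either method.

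**The case against.** The strongest reply is that nothing is wrong. Bonferroni is valid, fully specified and simple, and choosing it over Holm is not an error. It also has an advantage that Holm lacks: simultaneous confidence intervals that match its tests. Holm is not a one-word swap either, because pairwise tests follow each omnibus test and need a stated level once the omnibus thresholds vary. All of this stands. It makes the point an improvement with a small price, not a correction.

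It can also be said that the gain is modest. With proportional gains in the two torques it is about 3 percentage points for EPT, and it does not reach the comparison with both single arms. That stands too.

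A reader might go further and infer that the plan has no decision rule: that the hypothesis demands success on every outcome, the alpha split implies that any one suffices, and the objective counts only two. The article does not support this. The 0.05/3 threshold is a complete rule for a separate claim on each outcome, and such claims need no combined verdict. The hypothesis lists expected effects, including balance indices that the analysis section makes exploratory, so it cannot be read as a decision rule. H/Q is derived from flexor and extensor torque, so the objective is a loose summary rather than a competing definition. Sizing on one of several primary outcomes is ordinary practice. What remains is a wording gap.

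**Conclusion.** The multiplicity control is valid but less powerful than it could be. Under the stated f = 0.55 and 16 evaluable per arm, Holm raises EPT omnibus power from about 82% to between about 85% and 92%, with the same control of family-wise error and an unchanged chance of at least one significant outcome. The 82.5% and the 92.0% ceiling follow from the article's own inputs. The position between them rests on the assumed FPT gain, means, SDs and correlation.

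These are omnibus powers. They should not be read as probabilities of confirming that the combined arm is superior to each single arm. This is a worthwhile, inexpensive improvement; the wording of the objective and hypothesis is a supporting point.

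**What to change.** **Statistical analysis.** Replace the fixed p < 0.017 with Holm across the three primary omnibus tests: smallest p against 0.05/3, next against 0.05/2, largest against 0.05, stopping at the first failure. The same steps apply to a Kruskal–Wallis p-value where that test is used. State that the pairwise comparisons within each outcome remain Bonferroni-adjusted at a family level of 0.05/3. Each of the nine comparisons is then at 0.05/9, and 9 × 0.05/9 = 0.05 bounds the pairwise family-wise error.

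**Objectives and hypotheses.** Say that claims are made separately for each primary outcome, name H/Q in the primary objective, and move the balance indices out of the main hypothesis into the exploratory secondary one.

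**Cost.** No participants, visits or data. Holm has no simple matching simultaneous confidence intervals, so the report should say which intervals it gives. A change of analysis method goes to the ethics committee under the article's Protocol amendments section, and should be made before any outcome data are analysed.

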### Safety monitoring

Potential adverse events include muscle soreness, fatigue, dizziness, ankle or knee discomfort, falls, sprains, and other exercise-related injuries. Instructors will monitor participants during every training session and will terminate or modify exercises if participants report pain, dizziness, or excessive fatigue. All adverse events will be documented with onset time, severity, management, relationship to the intervention, and outcome. Serious adverse events will be reported to the ethics committee according to institutional procedures.

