### Participants

Healthy female college students will be recruited through the optional martial arts course and university announcements. Interested students will undergo eligibility screening and will provide written informed consent before enrolment (Table 1). Participants will be asked to maintain their usual diet and lifestyle during the study and to avoid initiating additional structured exercise programmes outside the assigned intervention.

**Table 1 tab1:** Eligibility criteria for study participants.

Eligibility domain	Criteria
Inclusion criteria	Female college students aged 18–22 years; normal physical examination; no history of heart, brain, or kidney disease; no recent sports injury; no regular exercise in the previous 3 months; ability and willingness to complete all tests and training; written informed consent; agreement to maintain usual diet and lifestyle.
Exclusion criteria	Abnormal body morphology or obvious limb defects that may affect testing; fracture, muscle injury, or comparable injury within the past 6 months; inability to complete the intervention because of leave, internship, transfer, or similar objective reasons; inadequate training attendance; poor compliance; any adverse condition judged by investigators to increase exercise risk.
Withdrawal criteria	(R1 Q4)Voluntary withdrawal; repeated non-attendance (defined as missing two consecutive training sessions or three cumulative training sessions); development of a condition that makes further participation unsafe (defined as the occurrence of acute exercise-related injury, severe joint pain, cardiovascular discomfort, dizziness, vomiting, or any other health problem judged by the investigator to preclude safe continued training); investigator decision based on participant safety.

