### Blinding

Because of the clear operational differences among the exercise interventions, participants and instructors cannot be blinded. However, outcome assessors, data entry personnel, and statistical analysts will be blinded to group allocation. Group codes will be retained until the main statistical analysis has been completed. This approach is intended to reduce measurement and analysis bias while preserving the feasibility of the intervention.

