### Adherence and intervention fidelity

Attendance will be recorded for every session. A participant will be considered adherent if she meets both of the following criteria:

(1) Training frequency adherence: Attendance rate ≥80%; (2) No major protocol deviation: defined as any unapproved change to the intervention content, duration, intensity, or progression that could systematically affect outcome measures, including but not limited to: (a) performing a different Tai Chi form than the 24-form simplified routine, (b) using unstable surfaces or resistance loads outside the prescribed progression in the URT protocol, (c) combining outside structured exercise programmes that interfere with the intervention effect, or (d) persistent incorrect movement patterns that, despite instructor correction, compromise training safety or fidelity. Minor deviations (e.g., occasional missed warm-up exercises, temporary heart rate outside the target zone for <10% of session time) will be recorded but will not automatically classify the participant as non-adherent.

Instructors will follow standardized checklists to ensure intervention fidelity. Heart rate and observations will verify exercise intensity and quality. Missed sessions will be followed up to support continued participation where safe.

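### Table 1, read literally, makes any dizziness a ground for withdrawal, while Safety monitoring lets the instructor stop or modify the exercise; no sentence links the two rules

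*Protocol article*

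**What the plan says.** Three places in the Protocol article bear on this.

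- **Participants, Table 1, Withdrawal criteria.** One criterion is a condition that makes further participation unsafe, "defined as the occurrence of acute exercise-related injury, severe joint pain, cardiovascular discomfort, dizziness, vomiting", and the list closes with "any other health problem judged by the investigator to preclude safe continued training". Joint pain carries a grade; dizziness does not. A decision by the investigator on safety grounds appears in the same cell as a separate criterion.
- **Safety monitoring.** "Potential adverse events include muscle soreness, fatigue, dizziness, ankle or knee discomfort" opens the list of expected events. The response is given to instructors, who "will terminate or modify exercises if participants report pain, dizziness, or excessive fatigue". Withdrawal is not mentioned.
- **Adherence and intervention fidelity.** A major deviation is "any unapproved change to the intervention content, duration, intensity, or progression that could systematically affect outcome measures". The section mentions neither dizziness nor changes made for safety.

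Under Blinding, "participants and instructors cannot be blinded". The roles named as blinded are these: "outcome assessors, data entry personnel, and statistical analysts will be blinded to group allocation". Investigators are not among them, and their status is not stated.

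**The concern.** Two stated rules attach different consequences to one symptom, and neither refers to the other. Under the first, the occurrence of dizziness is enough to withdraw the student. Under the second, an unblinded instructor acts within the session and may simply adapt the exercise.

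The choice of rule affects the data as well as safety handling. Withdrawal takes a student out of the per-protocol set and may cost her post-test measurement. Only the unstable resistance and combined arms train on balance pads and wobble boards, while the Tai Chi arm trains on stable ground. Symptoms of this kind could therefore differ in frequency between arms, and an ambiguous withdrawal rule could then produce losses that are related to treatment.

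**Working it through.** The plan gives no figure on this point and none is needed. The check is a comparison of the texts, then a trace into the analysis sets.

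**1. Trigger.** Table 1 is met by the occurrence of a listed event. Safety monitoring is met by a participant's report. Dizziness is ungraded in both. Pain is graded as severe joint pain in Table 1 and ungraded in Safety monitoring, so for pain the two rules can at least be told apart by severity. For dizziness they cannot.

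**2. Consequence.** Table 1: withdrawal. Safety monitoring: the exercise is terminated or modified. Termination is compatible with later withdrawal; modification makes sense only if training continues.

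**3. Does the closing clause of Table 1 settle it?** There are two readings of "severe joint pain, cardiovascular discomfort, dizziness, vomiting, or any other health problem judged by the investigator to preclude safe continued training".

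- *Judgement governs the whole list.* Dizziness then leads to withdrawal only if the investigator finds continued training unsafe, and the two sections form a graded sequence.
- *Judgement governs only the catch-all item.* Any dizziness then meets the criterion.

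Two features favour the second reading: investigator decision is already a separate criterion, and severity was written in for joint pain but not for dizziness. The phrase introducing the catch-all item favours the first, because it suggests that the listed items are problems of the same kind. The wording does not decide between them.

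**4. Trace for one student with a single brief episode.**

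| | Table 1, literal | Safety monitoring |
|---|---|---|
| Participation | Withdrawn | Exercise stopped or modified; may continue |
| Intention-to-treat set | Included | Included |
| Per-protocol set | Excluded, since the full intervention is not completed | Included if the full intervention is completed without major deviation; the effect of a modified session is not stated |
| Post-test strength and balance | Not stated whether measured | Measured as scheduled if she stays in |

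**5. If the post-test is missing.** Statistical analysis plans multiple imputation when data are considered missing at random. The predictors named are baseline strength, baseline balance indices, age, height and weight. No adverse-event or attendance variable is named, so a value lost because of a training symptom would be imputed without that information.

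**The case against.** The strongest reply is that the two rules act at different levels: the instructor takes an immediate step in the session, and withdrawal is a later decision about the participant. If the closing clause of Table 1 covers the whole list, there is no contradiction. The article also mentions an intervention manual and staff training in adverse event reporting, where escalation steps may be set out. This stands in part: the rules can be read as a sequence. But the article never says so, and the difficulty is two stated rules that diverge, which is more than operational detail left to a manual.

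It is also fair that the primary analysis keeps all randomized students whatever their adherence or withdrawal, and that per-protocol is a sensitivity analysis. That stands and limits the impact.

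Three stronger readings are tempting, and the documents do not support them.

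- A reader might infer a third consequence: that a safety modification is a major deviation. The definition covers only unapproved changes, and Safety monitoring itself provides for the modification. At most, the article does not expressly say that such a change counts as approved.
- A reader might infer that unblinded staff decide both steps. Lack of blinding is stated for instructors only. That the investigator is not listed as blinded does not show that the investigator is unblinded.
- A reader might assume a dizziness rate per session and set the resulting withdrawals against the dropout allowance. No rate is given. The exercise would also assume withdrawal after one episode, which is the point in dispute, and that withdrawn students go unmeasured, which is not stated.

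**Conclusion.** The point holds as an unresolved conflict between Table 1 and Safety monitoring. Followed literally, Table 1 would withdraw a student for one minor episode that Safety monitoring treats as manageable within the session. The effect is on consistency of withdrawal, on membership of the per-protocol set and, conditionally, on the amount of missing post-test data. Membership of the primary analysis set does not change.

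The size is unknown. It depends on how often dizziness occurs in each arm, how staff read Table 1, and whether withdrawn students are still tested; the article settles none of these. A difference between arms is plausible from the training surfaces but is not shown. The correction is worth making because it is cheap and removes an avoidable source of loss. Nothing here implies which clinical rule is right.

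**What to change.** Before training starts:

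1. Reconcile Table 1 with Safety monitoring. State which events lead to a session-level action, which lead to ending training, and who decides. The clinical thresholds are for the investigators to set.
2. State that participants who end training are still invited to the post-intervention assessment where safe.
3. In Adherence and intervention fidelity, state that a modification made under Safety monitoring is not an unapproved change.
4. Report stops and modifications by arm.

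The cost is wording in three sections, one field on the instructor form and, if the change counts as important under Protocol amendments, ethics committee review. No extra staff or visits beyond the scheduled assessment are needed. A small downside is that a few participants with modified training stay in the per-protocol set; the report by arm makes that visible.
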